## 1. Introduction

The COVID-19 pandemic has caused a profound transformation in the global healthcare landscape, resulting in over 5.6 million deaths [1]. It has also disrupted social and economic activities worldwide, affecting people’s mental health [2,3]. In response to the rapid spread of the virus, the global community prioritized the development of effective safety measures, with vaccines emerging as a central strategy to control the pandemic [4]. However, despite the availability of COVID-19 vaccines, vaccine hesitancy (VH)—defined as delay or refusal to accept the vaccine—has become a significant global challenge during COVID-19 pandemic [5,6]. The World Health Organization (WHO) identified VH as one of the top public health threats, with estimates suggesting that approximately 26% of the population exhibited resistance to the COVID-19 vaccination [7,8]. A comprehensive approach to addressing VH requires integrating demographic, social, environmental and psychological dimensions [7,9,10,11,12]. Examining these factors is important to combat hesitancy toward the COVID-19 vaccine, guide targeted interventions that sustain effective public health responses, and contribute to managing future pandemics [13]. For example, a systematic review of 23 studies identified key demographic and socioeconomic features influencing COVID-19 vaccine uptake [14]. Older age, higher income, and greater educational level were associated with higher vaccine acceptance [6,15]. Concerns about vaccine safety, distrust in pharmaceutical companies and governmental health policies, absence of prior influenza vaccination, and exposure to misinformation have been strongly linked to VH [6,16,17]. Moreover, religiosity has been associated with lower vaccine intent, particularly in communities were vaccine acceptance conflicts with cultural or religious beliefs [18]. From a psychological perspective, a large body of evidence has reported that individuals with paranoid tendencies, impulsivity, low conscientiousness or emotional instability exhibit greater VH [7,9,19]. Furthermore, dogmatic thinking patterns and reduced empathic capacity are correlated with increased reluctance toward vaccination [19,20,21]. Complementing these findings, a multinational study across 24 countries identified disgust sensitivity and anxiety toward medical procedures (e.g., injections) as critical psychological drivers of anti-vaccine attitude, alongside adherence to individualistic/hierarchical worldviews [9]. Notably, contextual factors such as needle phobia—prevalent in approximately 10% of the population—and maladaptive fear regulation mechanisms may further entrench avoidance behaviors, exacerbating VH [22]. Beyond psychological and contextual variables, political ideology has emerged as a debated determinant of vaccine attitudes. However, empirical evidence remains inconsistent: while some studies report a correlation between a conservative political orientation and increased VH [23], others find no statistically significant relationship [24].

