#### 2.1.1. Participants

A total of 40 healthy participants, aged 18 to 50 years, will be recruited for a randomized-controlled study and categorized based on their attitudes toward COVID-19 vaccination:Vaccine-Hesitant/Resistant Group (*n* = 20): Individuals reluctant to receive the COVID-19 vaccine, identified using validated psychometric tools, including the Vaccine Hesitancy Scale [26] and the Vaccine Hesitancy Scale for COVID-19 Vaccination [27].Vaccine-Accepting Group (*n* = 20): Individuals who are vaccinated or express no hesitation toward vaccination. They will serve as controls.

Recruitment will be conducted through online advertisements and university mailing lists. To ensure comparability, groups will be matched by demographic variables, including age, gender, and educational level.

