## 3. Discussion

This study aims to provide novel insights into the psychophysiological correlates of vaccine hesitancy (VH). Grounded in the Somatic Marker Hypothesis [25], we hypothesize that bodily and emotional responses will play a crucial role in shaping vaccination attitudes. By investigating sensorimotor mapping, affective learning processes, and psychological predictors of VH, we seek to contribute to a more comprehensive understanding of this phenomenon.

### 3.1. Experiment 1

We predict significant differences in motor evoked potentials (MEPs) between vaccine-hesitant and vaccine-accepting individuals when exposed to COVID-19 vaccination imagery. Specifically, hesitant individuals may exhibit reduced MEP amplitudes in the deltoid muscle—a key muscle involved in vaccine administration—suggesting altered sensorimotor resonance in response to vaccination stimuli. This would align with previous research on embodiment, which posits that motor responses are modulated by observed actions [48,49]. The sensorimotor resonance may serve as a proxy for embodied affective states such as disgust or fear—emotions that are central to the Somatic Marker Hypothesis, which emphasizes the role of visceral and emotional signals in guiding behavior and cognition [25]. Therefore, a decrease in MEP amplitude may indicate a disruption of somatic marker signals, given that corticospinal excitability is sensitive to modulation by negative emotional states. This interpretation is supported by prior work demonstrating the influence of emotions—particularly aversive or defensive states on motor system activity [39,40,41,50,51,52,53]. We suggest that motor resonance changes, in this context, may index the embodied affective experience central to the SMH, thereby linking motor excitability to emotional and interoceptive processing.

Additionally, we anticipate increased facial electromyography (EMG) activity in the levator labii superioris and corrugator supercilii muscles in vaccine-hesitant individuals, reflecting higher levels of disgust and fear responses. If confirmed, these results would support the hypothesis that VH is influenced by affective biases linked to disgust sensitivity and anxiety [9,21].

### 3.2. Experiment 2

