## Abbreviations

The following abbreviations are used in this manuscript:

COVID-19	Coronavirus Disease 2019
VH	Vaccine Hesitancy
MEPs	Motor Evoked Potentials
EMG	Electromyography
SCR	Skin Conductance Response
WHO	World Health Organization
Vax	Vaccinated individuals
No-Vax	Non-Vaccinated individuals
TMS	Transcranial Magnetic Stimulation
IQ	Intelligence Quotient
OSP	Optimal Scalp Positions
ECR	Extensor Carpi Radialis
rMT	Resting Motor Threshold
μV	Microvolt
mV	Millivolt
Hz	Hertz
3D	Three Dimensional
VR	Virtual Reality
EDA	Electrodermal Activity
dB	Decibel
ANOVA	Analysis of Variance
CS+	Conditioned Stimulus Positive
CS-	Conditioned Stimulus Negative
Tukey’s HSD	Tukey’s Honestly Significant Difference

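### Experiment 1: vaccination alone qualifies a person as a control, so hesitancy and experience of the depicted deltoid injection may be confounded, to an unknown extent, in the MEP contrast

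*Protocol article*

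**What the plan says.** Section 2.1.1 forms two groups of 20. The hesitant group is "Individuals reluctant to receive the COVID-19 vaccine, identified using validated psychometric tools", namely a general and a COVID-19-specific hesitancy scale. The control group is "Individuals who are vaccinated or express no hesitation toward vaccination. They will serve as controls". The Introduction describes hesitancy as "defined as delay or refusal to accept the vaccine".

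Participants are "recruited for a randomized-controlled study and categorized based on their attitudes toward COVID-19 vaccination". Despite the mention of randomisation, membership follows attitude and is not allocated. The matching variables named are age, gender and education.

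Section 2.8.1 analyses MEP amplitude with a 2 × 2 × 3 ANOVA: group (Vax vs No-Vax), muscle (deltoid vs extensor carpi radialis) and condition (blood, COVID-19, influenza), with no covariate. The Abbreviations expand the two group labels as "Vaccinated individuals" and "Non-Vaccinated individuals".

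The deltoid is the target because it is where vaccines are injected (Introduction). Section 3.1 expects lower deltoid MEPs in hesitant people viewing COVID-19 vaccination, "suggesting altered sensorimotor resonance in response to vaccination stimuli", and links this to somatic markers. It does not discuss prior vaccination.

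**The concern.** The article defines the groups in two ways that do not coincide: by attitude, through the scales, and by vaccination status, through the first half of the control criterion and the factor labels. The person in whom the two differ most usefully, someone vaccinated but hesitant, satisfies the control criterion through vaccination.

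This matters more here than in a questionnaire study. The stimulus is an injection into the upper arm and the outcome is the excitability of that muscle's cortical representation. Having had the depicted injection is a plausible rival explanation for a group difference. If status and attitude coincide, the group effect cannot be assigned to hesitancy. If hesitant people are placed among the controls, the contrast is also diluted.

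**Working it through.** **Inputs.** From the article: 20 per group and the entry rules (2.1.1), the MEP model (2.8.1) and the labels (Abbreviations). The article gives no figure on this point, so there is none to reproduce. Assumed, because not given: share with a previous COVID-19 injection among controls, pC = 60–100%, and among hesitant participants, pH = 0–40%; shift in a deltoid contrast due to experience, d = 0.5–1.0 SD.

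**Step 1. The four possible participants under the entry rules.**

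| Attitude | Status | Group under 2.1.1 | Fits the label in the Abbreviations? |
|---|---|---|---|
| accepting | vaccinated | control | yes |
| accepting | unvaccinated | control, by lack of hesitation | no, if coded Vax |
| hesitant | unvaccinated | hesitant | yes |
| hesitant | vaccinated | control by status; may also qualify as hesitant by scale | not if coded No-Vax |

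The second and fourth rows supply the overlap needed to separate attitude from experience. The labels do not fit the second row. The fourth row can be sent to the wrong side of the attitude contrast, and 2.1.1 does not say which criterion prevails.

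**Step 2. Dilution.** If k of the 20 controls are in fact hesitant and the true hesitant-minus-accepting difference is δ, the expected contrast is δ(1 − k/20). Assumed k = 1 gives 0.95δ; k = 4 gives 0.80δ.

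**Step 3. Confounding, with a true hesitancy effect of zero.** Expected apparent difference = d(pC − pH). For example, 0.8 × (0.80 − 0.20) = 0.48 SD. Rejection rates come from 20,000 simulated studies of 20 vs 20 with a two-sided t test at 0.05:

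| pC / pH | d = 0.5 | d = 0.8 | d = 1.0 |
|---|---|---|---|
| 60 / 40 | 0.10 SD, 5.8% | 0.16 SD, 7.2% | 0.20 SD, 8.0% |
| 80 / 20 | 0.30 SD, 14.7% | 0.48 SD, 29.2% | 0.60 SD, 40.6% |
| 100 / 0 | 0.50 SD, 33.7% | 0.80 SD, 69.4% | 1.00 SD, 86.7% |

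The test is two-sided, so the sign of d does not matter for these rates. With a real hesitancy effect present, experience could either inflate or mask it.

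**Step 4. What adjustment can recover.** With p = (pC + pH)/2, the squared correlation of group and experience is r² = [0.25(pC − pH)]² / [0.25 p(1 − p)], and effective N = 40(1 − r²).

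- 80/20: r² = 0.15² / 0.0625 = 0.36; effective N = 25.6
- 90/10: r² = 0.20² / 0.0625 = 0.64; effective N = 14.4
- 95/5: r² = 0.225² / 0.0625 = 0.81; effective N = 7.6
- 100/0: r² = 1; the two effects cannot be separated

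Overlap therefore has to be secured at recruitment.

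**Step 5. The design's own controls.** The extensor carpi radialis is not the vaccination muscle, so an effect of experience confined to the deltoid would also appear as group × muscle. Blood sampling involves a needle but is not a vaccination. The influenza condition cannot be assumed free of the problem, since the Introduction says that "absence of prior influenza vaccination, and exposure to misinformation have been strongly linked to VH". The scrambled picture is shown (2.7.1) but is not a level in the ANOVA.

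**The case against.** The strongest reply is that the operative definition is attitudinal and the Vax/No-Vax labels are shorthand. Hesitancy as delay or refusal lets late-vaccinated people count as hesitant, and the control criterion admits unvaccinated accepters, so overlap may be ample. This stands against three stronger readings a reader might infer:

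- That controls have mostly had the injection and hesitant participants mostly have not, or that the split is 100% to 0%. No vaccination proportions are given; these readings come from the labels alone.
- That experience would produce the same reduction in deltoid MEPs that the article predicts. Neither the direction nor the size of an experience effect is documented, and it could run the other way.
- That influenza exposure is known to differ between these groups. The Introduction reports a background association, not rates in this sample.

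The affective reading also has other support: vial pictures without an injection, facial EMG, emotion ratings, and correlations of MEPs with psychometric scores. Section 3.1 is hedged. These measure affect separately, but they do not tell attitude from experience in the deltoid contrast, and block is not a factor in the MEP ANOVA.

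Two further objections limit the remedy. Non-vaccination is partly what hesitancy means, so adjusting for it may remove some of the effect of interest. A comparison of vaccinated with unvaccinated people among only 20 hesitant participants is too small to support inference.

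It may also be said that history items and sensitivity models belong in the full protocol. That is fair for the detail. The entry rule, labels and model factors, however, are fixed in this article.

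**Conclusion.** The point holds as a flaw in how the groups are defined. Being vaccinated is sufficient for the control group, the factor is named for vaccination status, and the conclusion is to be drawn about attitude. In Experiment 1 attitude and experience of the depicted injection may be partly or wholly confounded, and vaccinated hesitant people can enter the control group.

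The extent of bias is unknown. The illustrative rejection rates run from near nominal (5.8%) to 86.7% according to assumed shares and an assumed effect. They come from a two-sample t test, not the planned ANOVA, so they show only that overlap matters and do not estimate this study's error rate. The documents do not establish that the groups are fully aliased or that the predicted result would arise from experience.

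**What to change.** - **Group assignment.** Assign both groups only by the hesitancy scales already named. Drop vaccination as a sufficient control criterion, so that vaccinated hesitant people enter the hesitant group. Section 2.2.1 repeats the rule for Experiment 2 and should be aligned.
- **Labels.** Rename the factor hesitant vs accepting in 2.1.2, 2.8.1 and the Abbreviations, and in the matching Experiment 2 sections.
- **Data.** Record COVID-19 and influenza vaccination history in the existing demographic questionnaire, and report status by group.
- **Analysis.** Add one sensitivity model for MEPs with condition-matched experience (ever had that vaccine, yes/no). Let its effect differ by muscle, since the group effect at issue is specific to the deltoid. Experience varies by condition, so this needs a mixed model; blood has no matching vaccine, so the two vaccine conditions are the natural scope. Label it exploratory, because non-vaccination is partly a consequence of hesitancy and precision will be low.
- **Reporting.** If overlap is too small, state that the deltoid group effect cannot be separated from injection experience. Do not base inference on a comparison within the 20 hesitant participants.

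The cost is a few questionnaire items, a wording change and one extra model. Stimuli, TMS procedure and sample size are unchanged. Finding vaccinated hesitant participants may take some recruitment effort.

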#### 2.1.2. Sample Size Calculation

The required sample size was determined a priori using GPower 3.1 [28], targeting the primary statistical analysis: a mixed-model ANOVA with 2 between-subjects groups (Vax vs. No-Vax) and 2 within-subjects factors—muscle (deltoid vs. extensor carpi radialis) and condition (Blood, COVID-19, Influenza). The analysis aimed to detect a medium effect size (f = 0.25), considered the smallest scientifically meaningful effect size [29], with a power of 0.95 and α = 0.05. Given the repeated-measures structure, the analysis assumed a moderate correlation (r = 0.5) between the six repeated measurements (2 muscles × 3 conditions), which reflects the expected level of association in related psychometric constructs such as disgust sensitivity and anxiety. This correlation value was specified in GPower to ensure accurate estimation. Under these parameters and assuming ideal sphericity (ε = 1), the required sample size was estimated at 40 participants.

### 2.2. Experiment 2

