#### 2.2.2. Sample Size Calculation

The sample size was determined a priori through power analysis using GPower 3.1 [28], targeting the primary statistical test: a mixed-model ANOVA with 2 between-subjects groups (Vax vs. No-Vax), and 2 within-subjects factors—stimulus (CS+ threat-associated stimulus vs. CS− safety-associated stimulus) and time (3 SCR measurements: habituation, acquisition, extinction recall). The analysis aimed to detect a medium effect size (f = 0.25), with 95% power at an alpha level of 0.05. A moderate correlation of r = 0.5 was assumed among the six repeated measurements (2 stimuli × 3 phases), based on prior psychophysiological research and expected consistency in responses influenced by individual differences in disgust sensitivity and anxiety. This correlation was explicitly specified in GPower to ensure accurate estimation. Under the assumption of ideal sphericity (ε = 1), a minimum of 40 participants is required.

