### 2.8. Statistical Methods

All statistical analyses will be conducted using Jamovi (version 2.6.23), an open-source statistical software based on the R 4.5.0 framework. A significant threshold of *p* < 0.05 will be applied to all analyses. Parametric methods will be employed under the assumptions of normality and homogeneity of variance, verified by Shapiro-Wilk or Kolmogorov-Smirnov and Levene’s tests, respectively. Non-parametric tests will be used if assumptions are violated.

#### 2.8.1. Experiment 1

A 2 × 2 × 3 mixed-design ANOVA will be conducted to analyze differences in MEP amplitudes, with group (Vax vs. No-Vax) as a between-subjects factor, muscle (deltoid vs. extensor carpi radialis), condition (Blood, COVID-19, influenza), as within-subjects factors.

EMG activity from the levator labii superioris (disgust) and corrugator supercilii (fear) will be analyzed using a 2 × 2 × 3 mixed-design ANOVA, incorporating group (Vax vs. No-Vax), muscles (levator labii superioris, corrugator supercilii), condition (Blood, COVID-19, influenza).

Significant interactions (*p* < 0.05) will be followed by Tukey’s HSD post hoc tests to identify condition-specific effects.

#### 2.8.2. Experiment 2

Habituation, fear acquisition, extinction, and recall will be assessed through Skin Conductance Response (SCR) amplitudes using a 2 × 2 × 3 mixed-design ANOVA. The analysis will compare responses to stimuli (CS+ threat-associated stimulus, CS− safety-associated stimulus) as a within-subjects factor, across groups (Vax vs. No-Vax) as a between-subjects factor and phases (habituation, fear acquisition, fear extinction) as a within-subjects factor. Similarly, subjective fear/disgust ratings (Likert scale) will be analyzed using a 2 × 2 × 3 mixed-design ANOVA, with group (Vax vs. No-Vax) as a between-subjects factor, and stimulus Type (CS+ vs. CS−) and phase (habituation, fear acquisition, fear extinction) as within-subjects factors. Significant interactions (*p* < 0.05) will be followed by Tukey’s HSD post hoc tests to identify condition-specific effects.

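### Experiment 1's 95% power rests on a correlation taken from questionnaire traits and names no target effect, and the ε = 1 assumed in both experiments is left out of the assumption checks

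*Protocol article*

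**What the plan says.** Section 2.1.2 bases the size of Experiment 1 on "a mixed-model ANOVA with 2 between-subjects groups (Vax vs. No-Vax) and 2 within-subjects factors—muscle (deltoid vs. extensor carpi radialis) and condition" (blood, COVID-19, influenza). The target is f = 0.25, "with a power of 0.95 and α = 0.05". For the covariance, "the analysis assumed a moderate correlation (r = 0.5) between the six repeated measurements (2 muscles × 3 conditions"), and the value is explained as one "which reflects the expected level of association in related psychometric constructs such as disgust sensitivity and anxiety". The conclusion follows: "assuming ideal sphericity (ε = 1), the required sample size was estimated at 40 participants". The section does not say whether a main effect or an interaction, and which one, was entered.

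Section 2.2.2 repeats the scheme for SCR, also with r = 0.5. It refers first to earlier psychophysiological research and then to individual differences in disgust sensitivity and anxiety. It ends: "Under the assumption of ideal sphericity (ε = 1), a minimum of 40 participants is required".

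Section 2.8 gives the assumption scheme for all analyses: "Parametric methods will be employed under the assumptions of normality and homogeneity of variance". It names a test for each of these two assumptions and non-parametric methods as the fallback. Sphericity does not appear, and neither does an ε correction. Condition (Experiment 1) and phase (Experiment 2) each have three levels.

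**The concern.** In a repeated-measures power calculation, r is the within-person correlation of the outcome across its cells. In Experiment 1 the outcome is the normalised MEP amplitude (Transcranial Magnetic Stimulation and Motor Evoked Potentials, under 2.6.1) in two muscles and three conditions. The association between disgust sensitivity and anxiety scores is a different quantity and carries no information about MEP error variance.

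The choice matters because r enters the error term of every test that involves group. A higher r raises power for interactions and lowers it for the group main effect, so r = 0.5 cannot be judged cautious or optimistic until the effect is named.

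The second covariance input, ε = 1, is the most favourable value possible. Section 2.8 verifies two other assumptions and leaves this one out. If the three-level tests were run without correction and sphericity failed, they would use too many degrees of freedom and reject too often.

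**Working it through.** **Inputs from 2.1.2:** two groups, m = 6 measurements, f = 0.25, α = 0.05, r = 0.5, ε = 1, N = 40 (20 per group, 2.1.1). The article gives no MEP or SCR correlation and no estimate of ε, so every other value below is an assumption.

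**Formulas (noncentral F, as in the G*Power repeated-measures routines):**
- Group-by-within interaction: λ = f²·N·m·ε/(1 − r), with df = (m − 1)ε and (N − 2)(m − 1)ε.
- Group main effect: λ = f²·N·m/(1 + (m − 1)r), with df = 1 and N − 2.

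**Step 1: the plan's own figure.**
- Six-measure interaction: λ = 0.0625 × 40 × 6/0.5 = 30, df 5 and 190, power 99.5%. N = 28 already reaches 95%.
- Three-level group-by-condition interaction (m = 3): λ = 0.0625 × 40 × 3/0.5 = 15, df 2 and 76, power 93.5%. N = 43 is needed, or 44 with equal groups.
- Group main effect: λ = 15/3.5 = 4.29, df 1 and 38, power 52%. N = 124 is needed.

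None of these returns 40. Of the variants tried, only one with four groups and six measurements gives exactly 40 (power 95.2%), and the design has two groups.

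**Step 2: sensitivity to r** (N = 40, ε = 1; values of r other than 0.5 are assumed).

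| r | Six-measure interaction | Three-level interaction | Group main effect |
|---|---|---|---|
| 0 | 85.5% | 67% | 96.5% |
| 0.2 | 93% | 77% | 76% |
| 0.3 | 96% | 83% | 67% |
| 0.5 | 99.5% | 93.5% | 52% |
| 0.7 | about 100% | 99.5% | 43% |

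The six-measure interaction keeps 95% down to r of about 0.27.

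**Step 3: sensitivity to ε** (N = 40, r = 0.5; values of ε below 1 are assumed).

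| ε | Six-measure interaction | Three-level interaction |
|---|---|---|
| 1 | 99.5% | 93.5% |
| 0.8 | 98.4% | 88.9% |
| 0.6 | 95.3% | 81.4% |
| 0.5 | 92.1% | 76.1% |

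A block pattern shows how ε could fall in Experiment 1. If r were 0.7 within a muscle and 0.3 across muscles (assumed), the mean r is 0.46, ε over the six cells is 0.56, and six-measure power is 92%.

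**Step 4: type I error of a three-level interaction with group.** Null data were simulated with 20 per group, r = 0.5 and assumed phase SD ratios. Independent runs of at least 20,000 data sets agree closely.

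| SD ratio | ε | Uncorrected F | Greenhouse-Geisser |
|---|---|---|---|
| 1:1:1 | 1 | about 5% | about 4.8% |
| 1:2:1 | 0.75 | 6.2% to 6.4% | 4.7% to 5.0% |
| 1:3:1 | 0.61 | 7.4% to 7.7% | 4.9% to 5.4% |

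Unequal phase variances are plausible in Experiment 2, because habituation has no aversive event and acquisition has one on 80% of CS+ trials (2.7.2). The article does not say how unequal they are.

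**The case against.** **Power.** On the most literal reading, a six-measure interaction, 40 is more than enough: power is 99.5%, and it stays at 95% or above down to ε of about 0.6 at r = 0.5. That stands. A reader might infer that Experiment 1 is underpowered, but the article does not show this. A badly sourced r is not necessarily a wrong one, and for interactions a larger true r would help. The 52% for the group main effect is also not evidence of a shortfall in the main hypothesis, because the MEP prediction in Discussion 3.1 concerns COVID-19 images and the deltoid, which is an interaction.

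**Type I error.** A reader might infer that the 5% level is broken. The article does not support that either. Section 2.8 is silent on correction and does not say that the F tests will be uncorrected, and a correction may sit in an analysis plan not shown. At ε = 1 the level holds. Effects whose within-subject part has only two levels (muscle, stimulus) and the group main effect are unaffected. The inflation in step 4 needs SD ratios that no section supplies, and it was computed for phase, not for log-transformed, normalised MEPs. What remains is narrower: 2.8 sets out which assumptions are checked and what follows if they fail, and it omits the one on which both sample sizes rest. Its stated fallback is not an ε correction.

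**Experiment 2.** It would be unfair to charge 2.2.2 with the same error, since it cites prior psychophysiological research, which is the right kind of source. The wrong basis belongs mainly to Experiment 1.

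**Conclusion.** The concern holds in a limited form. The reason given for r = 0.5 in 2.1.2 does not describe MEP amplitudes, the powered effect is not named, and the stated inputs do not lead to 40. The claim of 95% power is therefore unsupported, which is not the same as shown to be false. Depending on the effect meant, the stated inputs give anything from 52% to 99.5%. For the interactions alone the range is 93.5% to 99.5% at r = 0.5 and 83% to 96% at an assumed r = 0.3.

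The sphericity part is weaker and conditional. The 5% level for terms involving condition or phase is not guaranteed. The excess would be about 1 to 2.5 percentage points under the assumed SD ratios, and only if no correction is applied.

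The power figures assume the noncentral-F routines above, with f = 0.25 applied on the scale of whichever effect is tested.

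**What to change.** Keep 40 participants.

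1. **Section 2.1.2:** delete the psychometric rationale for r. Name the powered effect; the MEP prediction in 3.1 is an interaction of group with condition and muscle. Restate its power at 40 as a range over r and ε, taken from repeated MEP data where available and otherwise over a stated assumed range.
2. **Section 2.2.2:** restate the power in the same way for SCR amplitudes.
3. **Section 2.8:** report Greenhouse-Geisser corrected F tests for every within-subject term involving condition or phase, in both experiments (MEP, facial EMG, SCR and ratings).

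The cost is rewording and a re-run of the power calculation, with no added participants or procedures. The article does not show whether the group's earlier studies hold suitable deltoid and ECR data, hence the option of an assumed range. The downside is slightly lower power when sphericity holds, and a stated power that may look less favourable than 95%.

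### In both experiments N = 40 at 95% power does not follow from the stated inputs, and the 95% claim cannot stand for group differences in general

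*Protocol article*

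**What the plan says.** Section 2.1.2 (Experiment 1) says the calculation was done in GPower 3.1 for "a mixed-model ANOVA with 2 between-subjects groups (Vax vs. No-Vax) and 2 within-subjects factors", namely muscle (2 levels) and condition (3 levels). The inputs are f = 0.25, "with a power of 0.95 and α = 0.05", a correlation of 0.5 among the six muscle-by-condition measurements, and epsilon = 1. The result is that "the required sample size was estimated at 40 participants".

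Section 2.2.2 (Experiment 2) repeats these inputs for stimulus (2 levels) by time (3 levels) and concludes that "a minimum of 40 participants is required".

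Neither section says whether the powered effect is the group main effect, a within-subject effect or an interaction. Neither gives the effect-size option. No allowance for attrition or rounding is mentioned.

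Section 2.1.2 justifies r = 0.5 as a value "which reflects the expected level of association in related psychometric constructs such as disgust sensitivity and anxiety". Section 2.2.2 refers to earlier psychophysiological research as well as to disgust sensitivity and anxiety.

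The Discussion states the predictions. In Experiment 1, "hesitant individuals may exhibit reduced MEP amplitudes in the deltoid muscle" under COVID-19 vaccination imagery, with higher facial EMG activity in the same group. In Experiment 2, hesitant participants are expected to show higher SCR to CS+.

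**The concern.** A sample-size statement that lists all its numerical inputs should reproduce once the effect type is chosen. Here no choice of effect type on the GPower default scale leads to 40. The possible answers lie on both sides of it and far apart, so rounding cannot explain the gap.

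The gap matters because the 95% figure is stated for the ANOVA as a whole, while the power of that ANOVA at N = 40 differs greatly from one effect to another. The predictions concern differences between two groups of 20. A reader would take the 95% to cover them, and for several natural readings of those predictions it does not.

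The correlation is a separate weakness in Experiment 1. GPower needs the correlation among one person's repeated MEPs, and r strongly affects the result. The reason given concerns correlations between questionnaire constructs, which is a different quantity.

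**Working it through.** **Inputs** (sections 2.1.2 and 2.2.2, identical in both): k = 2 groups, m = 6 measurements, f = 0.25 (f² = 0.0625), r = 0.5, epsilon = 1, alpha = 0.05, target power 0.95. Sections 2.1.1 and 2.2.1 give 20 per group.

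**Step 1: attempt to reproduce 40.** GPower repeated-measures formulas, default effect-size scale, noncentral F:

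- Within effect or group-by-within interaction: λ = f²·N·m/(1 − r), with df = 5 and (N − 2)·5.
  - N = 26: λ = 0.0625 × 26 × 6/0.5 = 19.5, df 5, 120, power 0.936.
  - N = 28: λ = 21.0, df 5, 130, power 0.954. **Required N = 28.**
- Group main effect: λ = f²·N·m/(1 + (m − 1)r) = f²·N·6/3.5, with df = 1 and N − 2.
  - N = 122: λ = 13.07, power 0.948.
  - N = 124: λ = 13.29, power 0.951. **Required N = 124.**

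The stated 40 is not reproduced.

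**Step 2: variants.** All but the r = 0.3 row keep r = 0.5, and all keep epsilon = 1 and 95% power.

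| Variant (group-by-within interaction) | N required | Agrees with the text? |
|---|---|---|
| m = 3 | 44 (power 0.935 at N = 40) | no, six measurements stated |
| m = 2 | 54 | no |
| m = 4 | 36 | no |
| m = 6, SPSS-type option | 68 | option not stated |
| m = 6, Cohen-type option | 66 | option not stated |
| four groups, m = 6 | 40 (0.952) | no, two groups stated |
| r = 0.3, m = 6 | 40 (0.960; N = 38 gives 0.9496) | no, r = 0.5 stated |

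The last two rows show that 40 can be reached. They are only conjectures about how it arose.

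**Step 3: what N = 40 gives.**

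- Six-level interaction, default scale: λ = 0.0625 × 40 × 6/0.5 = 30, df 5, 190, power **99.5%**.
- Group main effect, f = 0.25: λ = 0.0625 × 40 × 6/3.5 = 4.29, df 1, 38, power **52.3%**.
- Group difference in one cell, d = 2f = 0.5, 20 versus 20: noncentrality 0.5 × √(20/2) = 1.58 on 38 df, two-sided power **33.8%**, before any Tukey adjustment. The smallest detectable d is about **0.91** at 80% power and **1.17** at 95%.

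**Step 4: the three-way term.** The ANOVA in section 2.8 is 2 × 2 × 3. Its group × within × within term has (2 − 1)(2 − 1)(3 − 1) = 2 df, not the 5 df obtained by treating the six cells as one factor. At N = 40, with df 2, 76:

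- SPSS-type specification: λ = f²·(N − 2)·2 = 0.0625 × 38 × 2 = 4.75, power **46.6%**.
- Default scale, f over three measurements: λ = 0.0625 × 40 × 3/0.5 = 15, power **93.5%**.
- Default scale, f over six cells: λ = 30, power **99.9%**.

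**Step 5: one predicted pattern, as an illustration.** Assume a group difference of d = 0.5 in the deltoid/COVID-19 cell only, with r = 0.5 and epsilon = 1. The noncentrality is λ = (20/2) × (sum of squared interaction deviations)/(1 − r).

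- 5-df test: sum = 0.25 × 5/6 = 0.208, λ = 4.17, power about 30%.
- 2-df three-way term: sum = 0.25 × 1/2 × 2/3 = 0.083, λ = 1.67, power about 19%.

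**The case against.** The strongest defence is that the plan targets a mixed ANOVA, and that the predictions are group-by-within interactions followed by post hoc tests. On the GPower default scale with the stated six measurements, N = 40 then gives 99.5%, so the study would recruit more than its inputs require. This stands for that effect on that scale. It does not explain 40, because the inputs then give 28. It also does not carry over to a difference confined to one cell, as step 5 shows.

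A second fair point is that single-cell contrasts are post hoc in section 2.8 and that the document never equates f = 0.25 with a single-cell d of 0.5. The 34% and the detectable differences therefore describe what 40 participants can show. They are not evidence of an arithmetic error.

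Four stronger readings are tempting and are not supported:

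- A reader might infer that the 95% claim attaches to no planned test. The document attaches it to the mixed ANOVA. What is missing is the effect within that ANOVA.
- A reader might quote only 47% for the three-way term. That needs an effect-size option the text does not mention, and other specifications give 93.5% or 99.9%.
- A reader might infer that a null result will be taken as evidence against a medium effect. No section commits the authors to that interpretation.
- A reader might fault the basis for r in both experiments. Section 2.2.2 already cites psychophysiological research, so the point holds for section 2.1.2 only.

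**Conclusion.** The sample-size statements are wrong as written in both experiments. The stated inputs give 28 or 124 depending on the effect, never 40, and nothing in the text bridges the difference. This rests on the GPower repeated-measures formulas with the default effect-size scale. The SPSS-type and Cohen-type options do not yield 40 from the stated inputs either.

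The unqualified 95% claim cannot stand for group differences in general, given how far power at N = 40 varies with the effect and the specification of f. It does not follow that the study is too small for every purpose. Whether 40 is enough depends on which effect the authors intend, and they have not said.

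In Experiment 1 the support for r = 0.5 concerns the wrong quantity. The value itself may or may not be reasonable for repeated MEPs; the document gives no data to judge it.

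**What to change.** In sections 2.1.2 and 2.2.2:

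1. Name the one effect that is powered (for example the group × muscle × condition term in Experiment 1) and the effect-size specification used in GPower.
2. Correct the inputs, or the N that results from them, so that the calculation reproduces.
3. Keep N = 40 and state the power it gives for the named effect.
4. Report the power or the minimum detectable difference for the predicted between-group contrasts. For one cell with 20 per group this is d of about 0.91 at 80% power and 1.17 at 95%.
5. Drop the unqualified 95% claim.

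In section 2.1.2 only, base r on the correlation among repeated MEPs of the same person, and show how the result changes over a plausible range of r.

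The cost is re-running one calculation and rewording two paragraphs. The stated power will look less favourable for between-group effects. Recruitment and the planned ANOVA do not change.
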